### Recruitment of project officers

At least three project officers will be recruited at each health facility from the existing health care providers (doctors/nurses/dieticians/health educators). Project officers will receive study specific training on the recruitment procedures, screening the participants, recording outcome measurements, and delivering the intervention to the patients.

All eligible patients in the selected health centers will be informed about the study by the project officers and invited to participate in the study. Interested patients will be screened for physical inactivity.

### Training of project officers

All project officers will be trained on study procedures and assessment tools. A Bespoke training on using pedometers and the app will be delivered by national experts in Oman (proposed dates March 2021). The training will target project officers who will deliver the consultations not those taking the study measurements.

### Blinding

Except for the socio-demographic data at baseline, all measures will be collected by nurses who will be blinded from the study objectives and group allocation. Owing to the nature of this study, the project officers may not be blinded completely from study objectives, however they will not be involved in data entry and/or analysis.

### Randomisation

The study is a 1 year 1:1 cluster randomized controlled trial of the lifestyle intervention versus usual care. A cluster randomisation design will be used to minimize between group contamination by having the two groups (intervention and comparison) from independent health centres. Group allocation will be generated using a random numbers table generated in SPSS v21done by an independent statistician at MOH. All health facilities (8) will be randomised to deliver either the intervention (*n* = 4) or usual care (n = 4). Health facilities will be informed of their allocation verbally by the project investigator and will receive an envelope containing invitation letter and project materials.

### Recruitment of patients

Recruitment will take place over a 2-month period. Inactive patients fulfilling the inclusion criteria will be provided with a participant information sheet about the study given by the project officers. Subsequently, an appointment will be given to all potential participants to attend a wellbeing clinic for baseline measures, linked to their diabetes clinic, within a week. A telephone call will be made to all willing participants to remind them of their appointment and ensure activation of the phone app. At the baseline visit the project officers will seek written informed consent and log any eligible individuals who decline participation (Fig. 1).

**Fig. 1 Fig1:**
[figure not shown]
Patient flow chart. CHF = control group. IHF = intervention group

Recruitment will be monitored on monthly basis and efforts to reduce loss to follow-up will be made by sending encouraging messages regularly to participants. Participants not attending their appointment will be called to consider rescheduling appointments, otherwise will be considered as withdrawal cases.

### Intervention group

All participants will receive the smart app that contains personalised PA and diet platforms, pedometer to measure weekly step counts and interactive platforms for peer motivation after registering them for to get an access username and password. In addition to that, patients will receive face to face visits to measure their anthropometric and metabolic parameters. Table 1 shows the timeline for each intervention component within the app.

**Table 1 Tab1:** Intervention components

Intervention visits	Weeks												
	0^**a**^	4	8	12^**a**^	16	20	24^**a**^	28	32	36^**a**^	40	44	48
**Phone physical activity and diet phone consultations**													
**Pedometer step counts**													
**Smart_LS Interactive phone App**													

^a^Point of intervention delivery

### Phone consultations

Recruited participants will be offered individual phone consultations (maximum 20–30 min) by the trained project officers on 4 occasions (0, 3, 6 and 12 months) on PA and healthy diet.

### Pedometer

Participants will be given a pedometer at their baseline visit. Instructions on how to use the pedometer, how to record their daily steps and how to set daily step goals will be discussed by the project officers. Participants will be asked to set individual goals and report their step count in the interactive phone application over the period of 12 months.

### Bespoke phone application for PA and healthy diet

Participants receiving the intervention will be asked to share a phone application in order to report their PA and diet behaviours step counts at baseline, 3, 6, 9 and 12 months. Participants will be encouraged to communicate with their respected project officers and their peers (optional). The application will be designed, and managed by experts from higher collage of technology in Oman.

### Usual care group

In the control arm, doctors will be allowed to continue the regular counselling and prescription for diet and physical activity according to current national guidelines and existing practices. In these conventional clinical consultations, healthcare is provided according to existing knowledge; counselling is given at the individual clinician’s decision. We will ensure a pragmatic comparator that reflect typical routine practice, which allows for useful comparison of the intervention to the existing care.

### Outcome measures/assessment instruments

Table 2 describes all relevant outcomes, tools used and time at measurement.

**Table 2 Tab2:** Outcome measures for pre-specified variables

Primary Outcome	Tool	When to measure	Type of variable
**Body weight (Kg)**	**Calibrated scales**	**B, 3F, 6F, 12F**	**continuous**
^**a**^**HbA1c (%)**	**Blood test (fasting sample)**	**B, 3F, 6F, 12F**	**continuous**
**Secondary Outcomes**			
**Socio-demographic data**	**Questionnaire**	**B**	**Binary / numerical**
**Height (m)**	**Stadiometer**	**B**	**continuous**
**Pedometer**	**Reporting step counts**	**B, 3F, 6F, 12F**	**numerical**
**GPAQ-MET-mins/week**	**Questionnaire**	**B, 3F, 6F, 12F**	**continuous**
**Diet assessment tool**	**Questionnaire**	**B, 3F, 6F, 12F**	**continuous**
**Lipid profile (mmol/l)**	**Blood test (venous fasted sample)**	**B, 3F, 6F, 12F**	**continuous**
**Blood pressure (mmHg)**	**Sphygmomanometer**	**B, 3F, 6F, 12F**	**continuous**
**Exit survey**	**Questionnaire (participants and project officers)**	**12F**	**description**

(B = baseline; 3F = 3 month follow-up; 6F = 6 month follow up; 12F = 12 month follow-up)

^a^while blood collection for HbA1c at 12 month is mandatory, it is only done at baseline, 3 and 6 month if missing from the electronic health information system or recorded within more than 4 months prior to the measurement visits

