### Secondary objectives

Estimate the impact on cardio-metabolic risk factors by measuring blood pressure and lipid profile at baseline and 12 months.

Estimate the impact on developing diabetes complications, by performing blood tests for kidney function, screen for retinopathy, diabetic foot exam findings at baseline and 12 months.

Estimate the impact of the intervention on change in PA and sitting time at 12 months follow up from baseline.

Estimate the impact of the intervention on the course of diabetes drugs/treatment plans at 12 months.

To examine the feasibility of the intervention (content, delivery and satisfaction) to the participants and care providers.

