### Sample size calculation

The study is powered to detect a change considered to be both meaningful and plausible on the primary outcome. A sample size of 392 (196 in each arm) will allow measuring a between group difference of 7% in BMI and 0.6%in HbA1c over 12 months from baseline, within a power of 80%, significance level of 5%, [19, 37] and a standardised difference of 0.394 (i.e. 0.394 of a standard deviation can be detected) under an Intra-cluster correlation coefficient of 0.01). With a drop-out rate of 20% and a recruitment rate of 70% the required sample size is 750 (375 in each arm). The equation below was used to calculate the sample size based on evidence from nearby countries, the UAE [38].

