### Statistical analysis

The analysis plan was adopted for a previous RCT on physical activity in diabetes in Oman [36]. Once all participants have been randomised, descriptive statistics including t-test for continuous variables and chi square for binary variables will be used to compare the two group’s variables at baseline. Descriptive analysis will also be used for summary statistics on patient assessment, eligibility, recruitment, withdrawal.

The primary outcome which is the rate of PA and healthy diet score, BMI and glycated hemoglobin over 12 months for all participants in both trial arms at 3, 6, and 12 months will be measured, summarized and tabulated for both study arms. Graphical illustration (box plots, histograms and bar charts) will be used where appropriate and the distributions of all outcome measures will be checked and transformed where appropriate. The main analysis will be linear regression modeling to test the main hypothesis related to the superiority of the proposed intervention in promoting healthy lifestyle compared with control group. All outcomes will be analysed adopting an intention-to-treat principle and all persons will be analysed in the groups to which they were randomised. We will try to minimize missing of data collected by ensuring complete and accurate data entry, however multiple imputation on the longitudinal data will be performed if we face missing data. For secondary analyses, logistic regression will be used adjusting for clustering of patients within health care facilitates.

Analysis and reporting of the results will follow the Consolidated Standards of Reporting Trials guidelines (CONSORT) for reporting RCTs [39]. SPSS version 21 will be used for data analysis.

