### Participant and public involvement

We will involve 2 to 3 patients with diabetes to share their perceptions and ideas about the practicality of using electronic applications in promoting healthy lifestyle. They are welcomed to join the study team meeting and discuss app components and outcome measures. The perspectives of caregivers will also be taken into consideration in testing and refining the study materials and procedures. At the end of the study, participants and care givers satisfaction with the intervention, including burden, will be assessed as part of the process evaluation.

Results of the main trial and other evaluation findings will be submitted for publication in international peer-reviewed journals and presented at international and regional scientific conferences and webinars.

Furthermore, the findings will be shared to the community through social media platforms to encourage community engagement in healthy lifestyle promotion.

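### The exit survey is timed at 12 months only, so participants who withdraw earlier are never asked about satisfaction and burden

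*Protocol article*

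**What the plan says.** The protocol article makes feasibility a secondary objective: "To examine the feasibility of the intervention (content, delivery and satisfaction) to the participants and care providers" (Secondary objectives).

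Table 2 lists one instrument that can carry the participants' own view, the exit survey. Its tool is given as "Questionnaire (participants and project officers", its variable type is descriptive, and its only time point is 12F, which the table key defines as "12F = 12 month follow-up".

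The section on participant and public involvement gives the same timing: "At the end of the study, participants and care givers satisfaction with the intervention, including burden, will be assessed as part of the process evaluation".

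Two other statements bear on who will still be there. The text below Fig. 1 says: "Participants not attending their appointment will be called to consider rescheduling appointments, otherwise will be considered as withdrawal cases". The sample size section states: "With a drop-out rate of 20% and a recruitment rate of 70% the required sample size is 750 (375 in each arm". No survey or interview at the time of withdrawal is described.

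**The concern.** An exit survey given at a fixed calendar point reaches only those who are still in follow-up at that point. Here that point is 12 months, and the plan expects a fifth of participants to be gone by then. The intervention asks for daily step recording, app reporting and repeated phone consultations over a year, so burden is a plausible reason for leaving. If it is one, the people with the most to say about burden are the ones not asked.

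The protocol's discussion wants the trial to inform scaling up to other regions. Acceptability measured in completers alone is a weak basis for that, and the loss cannot be repaired at the analysis stage. The multiple imputation mentioned under Statistical analysis is meant for the longitudinal data. For a survey given once, at 12 months, no early leaver would have an observed answer on which an imputation could be built.

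**Working it through.** **Inputs from the protocol article**
- Drop-out: 20%, a trial-wide planning allowance (Sample size calculation). It is stated, not derived, so there is no figure to reproduce for it.
- Evaluable sample: 392, or 196 per arm; stated total 750, or 375 per arm; recruitment rate 70% (same section).
- Survey timing: 12 months only (Table 2), with end-of-study timing repeated in the text.

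**Inputs assumed**
- Satisfaction of 80% in completers and 20% to 90% in leavers. The protocol gives no satisfaction figures; these values only show the scale.
- Every completer answers and no leaver does.

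**How many would be missed per arm**
- Enrolment that leaves 196 after drop-out: 196 / 0.8 = 245; missed 0.20 × 245 = 49.
- If 375 is the number approached and 70% enrol: 375 × 0.7 = 262.5; missed 0.20 × 262.5 = 52.5.
- If 375 is the number enrolled: missed 0.20 × 375 = 75.

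So about 49 to 75 intervention participants would not be surveyed, if the trial-wide 20% applies to that arm.

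**Error in the reported figure**

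Let d be the share not surveyed, C the satisfaction among completers and L that among leavers. Satisfaction among all who started is (1 − d) × C + d × L. The survey reports C. The overstatement is therefore C − [(1 − d) × C + d × L] = d × (C − L).

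With C = 80% and d = 0.20:

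| Leavers (assumed) | All who started | Reported | Error (points) |
|---|---|---|---|
| 80% | 0.8 × 80 + 0.2 × 80 = 80% | 80% | 0 |
| 60% | 64 + 12 = 76% | 80% | +4 |
| 40% | 64 + 8 = 72% | 80% | +8 |
| 20% | 64 + 4 = 68% | 80% | +12 |
| 90% | 64 + 18 = 82% | 80% | −2 |

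The extreme bounds, with all leavers dissatisfied or all satisfied, are 64% and 64 + 20 = 84%. That is a width of 20 points, equal to the unsurveyed share.

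**Sensitivity to drop-out.** For leavers at 40%, the error is 0.10 × 40 = 4 points at 10% drop-out and 0.30 × 40 = 12 points at 30%.

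**What a survey at withdrawal would gain.** If half the leavers answered (an assumption), the unsurveyed share would fall from 20% to 10%, and the width of the extreme bounds from 20 to 10 points.

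**The case against.** The strongest reply has four parts.

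1. A reader might infer that anyone who gives up the app, pedometer or calls is lost to the survey. The protocol does not support that. It defines withdrawal by missed appointments that are not rescheduled, and it keeps participants in their allocated group: "All outcomes will be analysed adopting an intention-to-treat principle and all persons will be analysed in the groups to which they were randomised". Someone who stops using the app at month 4 but attends at 12 months is still due the survey and can report the burden. This part stands, and it limits the point to people who leave follow-up.

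2. A reader might also infer that satisfaction will certainly be overstated. The protocol gives neither satisfaction figures nor reasons for leaving. People may go for reasons unrelated to the intervention, in which case the error could be nil or slightly negative. This stands too: the upward direction is likely, not established. The 20% is also an allowance for both arms together, and the intervention arm's own rate is not given.

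3. Feasibility has other planned sources: summaries of withdrawal, attendance sheets, checks on 10% of consultation notes, step counts and app reports during the year, and the project officers' own survey. These would reveal early disengagement, so the survey is not the sole answer to the objective. None of them, however, records what leavers themselves thought of the intervention or how burdensome they found it.

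4. The process evaluation may be set out in a fuller document, and the endpoint is secondary and descriptive. That justifies a low priority. It does not remove the point, because the 12-month timing is a rule the article states in two places, not a detail it leaves open.

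**Conclusion.** The point holds in a limited form. Followed as written, the schedule obtains no answer on satisfaction or burden from participants who withdraw from follow-up before 12 months, for whom the plan allows 20%. The reported results would describe completers. At 20% drop-out and an assumed 80% among completers, the error runs from 0 to 12 points upward as leavers' satisfaction falls from 80% to 20%, and it is 2 points downward if leavers are at 90%. These sizes rest on assumed satisfaction rates, on applying the trial-wide drop-out to the intervention arm, and on full response among completers.

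No sample-size figure or primary analysis is affected. This is a cheap improvement to a secondary, descriptive outcome.

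**What to change.** Change the exit-survey timing in Table 2 to *12F, or at withdrawal if earlier (offered by phone during the existing non-attendance call)*, and align the sentence on satisfaction and burden in the participant involvement section. Add one item on the main reason for leaving. Report satisfaction and burden with the response rate and with all who started the intervention as denominator, showing completers and leavers separately.

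The cost is one short questionnaire for about a fifth of intervention participants, in a call that is already planned for non-attenders. Only partial response from leavers can be expected, which is why the response rate must accompany the result. The change should be in place before follow-up begins, because leavers' answers are hard to obtain later.

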#### Sociodemographic information

A multi-section questionnaire will be available in the app will be used to interviewing the participants and collect basic information including gender, willayat, age, marital status, education, income, and job.

#### Physiological (medical history) data

This will include duration of diabetes, BMI, blood pressure, lipid profile, and presence of any comorbidities defined as cardiovascular, hyperlipidemia, thyroid abnormalities, renal, eye, musculoskeletal, or any other recorded condition in the electronic health information system coinciding with diabetes. Drug (treatment) history: type and dose will also be recorded.

#### Primary outcome

##### Physical activity

The Global PA questionnaire (GPAQ) will be used to assess physical activity based on time period shown in Table 1.

##### Nutrition assessment

Medical nutrition therapy for diabetes mellitus (MNT for diabetes) survey will be and nutrition status will be described in scores.

##### Body mass index

Every patient will have their weight and height measured using standardized and calibrated scales available in health centers at 4 time points (Table 1). In addition to that, waist circumference will also be measured using a measuring tape. The measurements will be taken by trained project nurses.

##### Glycated hemoglobin level (HbA1c)

Every patient will have their HbA1c level measured. Blood sample will be drawn by the project nurse, using sterilized vacutainers and samples collect in purple topped tube. Standardized and calibrated laboratory machines will be used to measure HbA1c level.

### Data collection and management

To evaluate the primary and secondary outcomes, all relevant data will be collected by the assigned project officers for data collection. Data will be recorded as described earlier at specified time points after randomisation. Drug history will be obtained from electronic records where available.

### Sample size calculation

The study is powered to detect a change considered to be both meaningful and plausible on the primary outcome. A sample size of 392 (196 in each arm) will allow measuring a between group difference of 7% in BMI and 0.6%in HbA1c over 12 months from baseline, within a power of 80%, significance level of 5%, [19, 37] and a standardised difference of 0.394 (i.e. 0.394 of a standard deviation can be detected) under an Intra-cluster correlation coefficient of 0.01). With a drop-out rate of 20% and a recruitment rate of 70% the required sample size is 750 (375 in each arm). The equation below was used to calculate the sample size based on evidence from nearby countries, the UAE [38].

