**Methods:**

A one year 1:1 cluster randomized controlled trial will be utilized to compare the use of phone consultations, a multi component interactive phone application and pedometers with the usual diabetes care on promoting PA and healthy diet. Participants will be screened for inactivity and should be T2D, aged18–65 years, and overweight or obese. Eight primary centers will be randomly selected in each arm (*n* = 375). The primary outcome is the between arms differences in PA and diet scores, BMI and HbA1c over 12 months from baseline. Additionally, secondary outcomes will include cardiovascular outcomes (BP, and lipids).

The trial has received ethical approval from the Omani Research and Ethical Review and Approval Committee. All eligible participants will be invited to their respected health centers to provide informed consent.

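### The stated rates turn 392 into 700, not 750; 750 is not labelled as approached or enrolled, the facility count is 8 or 16, and the cluster size and degrees of freedom behind the 80% power are not given

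*Protocol article*

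**What the plan says.** The section Sample size calculation gives the base figure as "A sample size of 392 (196 in each arm"), with "within a power of 80%, significance level of 5"%, "a standardised difference of 0.394 (i.e. 0.394 of a standard deviation can be detected") and an intra-cluster correlation coefficient (ICC) of 0.01. It then inflates: "With a drop-out rate of 20% and a recruitment rate of 70% the required sample size is 750 (375 in each arm"). It refers to an equation that does not appear in the text available. The prose gives no cluster size, number of clusters, design effect or degrees of freedom.

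On the number of facilities, the abstract says "Eight primary centers will be randomly selected in each arm" and attaches n = 375. The Randomisation section says "All health facilities (8) will be randomised to deliver either the intervention" or usual care, four to each. Study setting also has eight facilities in total.

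Nowhere does the protocol say whether 750 is the number to approach or the number to enrol.

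**The concern.** Three of the figures that define the trial's size do not fit together: the inflated target, what that target counts, and the number of randomised units. Recruitment is to be finished in two months. The eight facilities could aim to enrol 490 patients (392 allowing for drop-out), 525 (70% of 750 approached) or 750, which is about 61, 66 or 94 per facility.

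The facility count matters more than the patient count for precision in a cluster trial. With only four facilities per arm, the power also depends visibly on which cluster size and which reference distribution were used, and the prose states neither.

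**Working it through.** **Inputs.** From Sample size calculation: 392 analysed (196 per arm), 80% power, 5% significance, 0.394 SD, ICC 0.01, 20% drop-out, 70% recruitment, target 750. From Study setting and Randomisation: 8 facilities, 4 per arm. From the abstract: 8 per arm. The protocol does not state sidedness; two-sided is assumed throughout.

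**1. Reproducing 196 per arm.** Without clustering, n = 2 × (1.96 + 0.8416)² / 0.394² = 101.1 per arm (102 rounded up). With m patients per facility the design effect is 1 + (m − 1) × 0.01.

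- The design effect that gives 196 is 196/101.1 = 1.94, so m is about 95.
- m = 750/8 = 93.75: design effect 1.93, giving 195 per arm (197 if 102 is used). This reproduces 196.
- m = 392/8 = 49: design effect 1.48, giving 150 to 151 per arm.
- m = 750/16 = 46.9: design effect 1.46, giving 148 to 149 per arm.

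So 392 fits eight facilities in total and a cluster size of about 94. It does not fit sixteen facilities, and 94 is not the cluster size if 392 patients are analysed.

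**2. Inflation.** 392/0.80 = 490 enrolled; 490/0.70 = 700 approached. The stated 750 is 7% higher (750/700 = 1.071). Other ways of applying the two rates do not give it either:

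- 392 × 1.5 = 588
- 392 × 1.2 × 1.3 = 612
- 392/0.8 × 1.3 = 637
- 392 × 1.2/0.7 = 672
- 392/0.5 = 784

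In reverse, 750 × 0.70 = 525 enrolled and 525 × 0.80 = 420 completers. If 750 is instead the number enrolled, 750 × 0.80 = 600 are analysed.

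**3. Power for 0.394 SD, 4 facilities per arm, ICC 0.01.** SE = √(2 × design effect / n per arm); noncentrality = 0.394/SE; degrees of freedom = 8 − 2 = 6. For 392 analysed, SE = √(2 × 1.48/196) = 0.123 and noncentrality = 3.21.

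| Analysed | Per facility | Design effect | Power, t on 6 df | Power, normal |
|---|---|---|---|---|
| 392 | 49 | 1.48 | 76% | 89% |
| 420 | 52.5 | 1.515 | 78% | 91% |
| 600 | 75 | 1.74 | 86% | 96% |

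By the 6-df t test, 80% needs about 456 analysed. With 8 facilities per arm and 392 analysed (24.5 each, design effect 1.235, 14 df), power would be 90% by t and 94% by the normal formula.

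**4. Sensitivity to the ICC.** The protocol gives only 0.01. At an assumed 0.02, power by t on 6 df is 64% at 392 analysed and 72% at 600 (normal: 80% and 87%). At an assumed 0.05 it is 43% and 46%.

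**The case against.** The strongest reply has four parts.

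- **The 392 is not wrong.** It reproduces with 750/8 patients per facility, and a larger assumed cluster size is conservative: with 49 per facility the normal formula needs only about 150 per arm. This stands. What remains is that the cluster size is unstated and does not match 392 analysed.
- **The 750 slip does no harm.** It leaves 420 completers, more than 392. This stands as to direction. It does not settle whether 750 is approached or enrolled.
- **The facility conflict resolves itself.** Two Methods sections agree on eight, and the base figure fits eight. This largely stands, so the abstract is the text to correct.
- **The power is not shown to be below 80%.** A reader might infer that four facilities per arm give 76% power and that the trial is underpowered. The document does not support that as an unconditional statement. The 76% needs exactly 392 analysed, 49 per facility and a t reference on 6 df; the target of 750 gives 78% to 86% by the same test, and the normal formula gives 89% or more. Nor can it be asserted that the calculation used normal quantiles. Step 1 shows that they reproduce 196, but the equation cannot be seen.

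**Conclusion.** The point holds in limited form. Three defects are certain from the text: the stated rates give 700 and not 750; the target is not labelled although a recruitment rate has been applied to it; and the abstract's eight centres in each arm contradicts eight in total. The first errs on the safe side by 50 patients approached, or 28 completers (420 against 392).

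The power issue is conditional. With eight facilities, ICC 0.01, equal cluster sizes and a two-sided 5% t test on 6 df, power for 0.394 SD is 76%, 78% or 86% at 392, 420 or 600 analysed. Whether the stated 80% is met therefore depends on what 750 means and on the reference distribution, and it falls quickly if the ICC exceeds 0.01. The ICC values above 0.01 are assumptions for display, not figures from the protocol.

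**What to change.** - In the abstract, state 4 facilities per arm, 8 in total.
- Give approached, enrolled and analysed numbers separately. Either correct 750 to 700 approached (490 enrolled, 392 analysed), or state that 750 is the number to enrol (600 analysed), or state that 750 is a deliberately rounded-up approach target (525 enrolled, 420 completers).
- State the cluster size, design effect and degrees of freedom used.
- Restate the power for the chosen analysed number with 6 df: 76% for 392, 78% for 420 or 86% for 600. Add its sensitivity to the ICC, for example 64% at 392 and 72% at 600 for an assumed ICC of 0.02.

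The cost is one paragraph and one line of the abstract. The stated power may become slightly less favourable. Restating it needs no extra patients. Holding 80% on the 6-df test would be a separate decision: about 456 analysed, which is 456/0.80 = 570 enrolled and 570/0.70 = about 814 approached. Enrolling 750 would already cover that.
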